#### RQ5: expert rating

4.2.6

The best-performing NLP model will be retrained with optimized hyperparameters on the full dataset, excluding the expert-rated entries. Model and expert performance will be compared on item-level absolute errors using RMSE, MAE, and Spearman’s ρ, with parametric or nonparametric pairwise tests applied as appropriate. Effect sizes and 95% confidence intervals will be reported, and bootstrap confidence intervals will supplement differences in MAE and RMSE.

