## Research questions and hypotheses

2

Building upon the illustrated gaps in current research, this study investigates the potential of NLP applied to digital journaling data with the aim of monitoring and supporting students’ emotional well-being, while generating individualized feedback on the journaling content and evaluating the students’ preferences.

Primarily, we hypothesize that (RQ1) emotional well-being and stress levels can be predicted from journaling entries using NLP. Prediction accuracy is expected to be higher for spoken entries (transcribed speech) compared to typed entries. Secondly, we hypothesize that (RQ2) the participants will evaluate the individualized feedback positively, indicating its acceptability and potential to foster reflection and compliance. Thirdly, we expect (RQ3) higher *state self-control* and *trait self-control* to be associated with greater adherence to the study protocol, and will be negatively correlated with dropout rates.

Furthermore, we will undergo (RQ4) an exploratory analysis of the improvement of the students’ emotional well-being over the study period, including the difference when typing vs. speaking the journal entries. Lastly, (RQ5) the predictive performance of NLP models will be compared to that of human experts (psychotherapists and clinical psychologists) in an exploratory manner to gain a practical perspective on the models’ performance. If RQ1 and RQ2 should hold true, future work should proceed to explore the usage of NLP to provide feedback automatically.

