### Expert rating

3.7

To put the NLP model performance into relation to human performance, we will implement an online survey using the SoSci Survey platform for exploratory comparison. Licensed psychotherapists and clinical psychologists will be recruited via email invitations. Each participant will evaluate the well-being and stress levels of 24 anonymized journal entry samples by estimating the three MDBF subscales and the PSS-4 score. The number of items are chosen to keep the completion time around 45 min (approx. 1.5 min per entry). The presentation order will be randomized between participants. Ratings will have to be made on continuous sliders (one-decimal precision), ranging from the minimum to maximum values of the respective questionnaires. This format ensures direct comparability with the model predictions, which also yield decimal outputs. As an incentive, participants will receive feedback at the end of the study: the journal entries will be presented again, along with their corresponding ground truth values, allowing the experts to compare their own assessments to the actual scores.

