#### RQ1: NLP analysis

4.2.2

The spoken journal entries will be transcribed using Whisper [65]. All journal entries will be preprocessed according to standard NLP procedure (tokenization, lowercasing, lemmatization, and stop-word removal) to generate sparse representations [e.g., term frequency–inverse document frequency; TF–IDF). Additionally, dense representations (e.g., contextual embeddings from German pre-trained transformer-based models like GBERT [66] or German-BERT [67]] will be generated. Here, preprocessing will be limited to the model-specific tokenization procedure.

The comparison of architecture classes is itself part of the study, as prior literature has not yet established a best-performing architecture for journaling data. Therefore, different supervised machine learning models will be employed for this regression task, ranging from classical approaches (e.g., random forest regression or support vector regression) to transformer-based deep learning models (e.g., BERT-based regression head). Separate predictive models will be trained on the above-mentioned representations for each outcome variable (MDBF subscales, PSS-4). We will additionally evaluate end-to-end fine-tuning of a smaller transformer model (e.g., a distilled German BERT variant), which will operate directly on tokenized journal entries rather than precomputed representations. Here, we acknowledge the higher risk of overfitting compared to our main representation-based approach.

As a baseline, a mean predictor will be implemented. Model performance will be quantified using root mean squared error (RMSE) and mean absolute error (MAE) to capture prediction error magnitude, and Pearson correlation to assess the strength of association between predicted and observed scores. All models will be evaluated using k-fold cross-validation. To account for repeated measures within participants, cross-validation will be conducted at the participant level, such that all entries from a given participant are assigned exclusively to either the training set or the test set. To examine group differences, models will be trained and evaluated separately for the written and transcribed groups. Predictive performance metrics will then be compared across groups. Differences in performance will be formally tested using bootstrapped confidence intervals to provide robust inference without assuming normality of error distributions.

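### RQ5 holds out only the expert-rated entries, not their authors, so the exploratory model-versus-expert comparison may favour the model

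*Protocol article*

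**What the plan says.** Section 3.7 (Expert rating) describes the expert task: "Each participant will evaluate the well-being and stress levels of 24 anonymized journal entry samples". The true scores come only at the end, when "the journal entries will be presented again, along with their corresponding ground truth values". The section does not say how many participants the 24 entries come from.

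Section 4.2.6 (RQ5) fixes the model side: "The best-performing NLP model will be retrained with optimized hyperparameters on the full dataset, excluding the expert-rated entries". The two sides are then set against each other on the same items: "Model and expert performance will be compared on item-level absolute errors using RMSE, MAE, and Spearman’s ρ".

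Section 4.2.2 (RQ1) uses a different separation rule and gives the reason: "To account for repeated measures within participants, cross-validation will be conducted at the participant level", so that "all entries from a given participant are assigned exclusively to either the training set or the test set".

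Section 2 gives the status of RQ5: NLP performance "will be compared to that of human experts (psychotherapists and clinical psychologists) in an exploratory manner".

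**The concern.** Entries by one student are not independent. They share recurring people, topics and phrasing, and the scores attached to them share that student's usual level of mood and stress. RQ1 guards against a model exploiting this. RQ5, as worded, does not: after a rated entry is removed, the author's remaining entries and their labels can stay in training.

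The advantage runs one way. The model can link an author's style to that author's usual scores. The expert receives anonymized entries and no labelled history. A model could then match or beat clinicians partly by recognising who is writing rather than by reading how the day went. Confidence intervals on the error difference would not reveal this, because it is a bias and not sampling noise.

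At stake is the practical benchmark that section 3.1 assigns to RQ5. Any later automatic feedback would have to work for students the model has never seen.

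**Working it through.** **Inputs from the protocol.** Section 4.1: 500 data points per group, 14 days, 28% dropout, 50 participants per group. Section 3.7: 24 rated entries. The protocol gives no intraclass correlation (ICC) for the daily scores and no measure of how recognisable authors are in their text. Both are assumptions below.

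**Step 1: the plan's own figure.** N = D / (d × (1 − r)) = 500 / (14 × 0.72) = 49.6, rounded up to 50 per group. Reproduced.

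**Step 2: entries left in training.** Expected entries per participant are 14 × 0.72 = 10.08, at most 14. If one entry per author is rated, about 10 − 1 = 9 labelled entries by that author remain, at most 14 − 1 = 13. None remain only if every entry by each rated author is among the 24 (for instance two authors with 12 entries each), which the protocol does not state.

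**Step 3: upper bound.** Suppose the model recognises the author fully and has m = 9 other labelled entries. With outcome variance 1:

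- reliability of the author's level = m × ICC / (1 + (m − 1) × ICC)
- RMSE ratio (author known / author unseen) = √(1 − ICC × reliability)
- correlation from author level alone = √(ICC × reliability)

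For ICC 0.3: reliability = 2.7 / 3.4 = 0.794; ratio = √(1 − 0.238) = 0.87; r = √0.238 = 0.49.

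| Assumed ICC | Reliability | RMSE ratio | RMSE reduction | r with no day-level signal |
|---|---|---|---|---|
| 0.2 | 0.69 | 0.93 | 7% | 0.37 |
| 0.3 | 0.79 | 0.87 | 13% | 0.49 |
| 0.4 | 0.86 | 0.81 | 19% | 0.59 |
| 0.5 | 0.90 | 0.74 | 26% | 0.67 |

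The percentage reductions are unchanged if the text also explains 10% or 30% of both the between-author and the within-author variance.

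**Step 4: simulation with imperfect recognition.** 100 authors with 10 entries each, 60 text features, kernel ridge regression, 24 test entries from 24 different authors, 60 runs per setting. Training excluded either the 24 entries only or all entries by those 24 authors. Author style was absent, moderate (author SD half the entry-level SD) or strong (equal SDs).

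| ICC | Author style | MAE, entries excluded | MAE, authors excluded | Reduction |
|---|---|---|---|---|
| 0 | none | 0.729 | 0.729 | 0% |
| 0 | strong | 0.752 | 0.782 | 4% |
| 0.3 | none | 0.718 | 0.723 | 1% |
| 0.3 | moderate | 0.728 | 0.766 | 5% |
| 0.3 | strong | 0.672 | 0.774 | 13% |
| 0.5 | none | 0.691 | 0.700 | 1% |
| 0.5 | moderate | 0.705 | 0.754 | 7% |
| 0.5 | strong | 0.667 | 0.822 | 19% |

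In the last row the correlation is 0.57 against 0.19. Part of each gap reflects the smaller training set when authors are excluded. The 4% at ICC 0 with strong style shows that the gap is not all recognition of an author's level.

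**Step 5: model choice and tuning.** Section 4.2.2 evaluates all models by cross-validation and sets no entries aside for RQ5. Section 4.2.6 does not say on which data the best model and its hyperparameters are chosen. The rated entries may therefore have entered those steps too.

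**The case against.** **Status.** RQ5 is labelled exploratory, and section 2 makes the move to automatic feedback depend on RQ1 and RQ2. RQ1 keeps its participant-level split and already gives an estimate for unseen students. This stands and limits the severity.

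**Size.** The upper bound assumes perfect recognition and compares an author's level with the grand mean; it is not a measured advantage over experts. Stop-word removal and lemmatization, planned for the sparse representations, strip some style. With no author style in the text the simulated gap is about 0 to 1%. This stands: the direction is clear, the size is not known.

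**Sampling of the 24 entries.** An article may leave this to a fuller plan, so its absence is not itself a fault. But the exclusion rule is stated outright, and it is safe only under one unusual sampling scheme.

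**Two stronger readings that the text does not support.** A reader might infer that the retrained model pools both groups and was never evaluated, since RQ1 trains separately by group. But the full dataset may equally mean all folds rather than both modalities, and the separate training is given for the purpose of examining group differences. The wording is ambiguous, no more. A reader might also infer that tuning certainly used the rated entries. The protocol only leaves this open, and 24 of about 1,008 entries (2.4%) would have limited influence on selection.

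**Conclusion.** The point holds in a limited form and should be fixed; it is not critical to the trial. RQ5 excludes by entry where RQ1 separates by participant, and no reason is given for the difference. Followed as written, and unless all entries by each rated author are among the 24, the model can use labelled entries by the same authors that the experts do not have. The benchmark may then favour the model and would not carry over to a new student.

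The protocol does not fix the size. The illustrative range is 0 to 19% lower MAE in simulation, at assumed ICCs of 0 to 0.5 and author style from absent to strong. The upper bound is 7 to 26% lower RMSE at assumed ICCs of 0.2 to 0.5 with full recognition and 9 other entries per author. The documents do not support saying that the model will win by recognising authors, only that the design cannot rule it out. RQ1 is unaffected.

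**What to change.** Replace the retraining sentence in section 4.2.6 with wording such as: *For each expert-rated entry, the model prediction is the participant-level out-of-fold prediction, from a model whose training data contain no entry by that participant; tuning and model selection are nested so that they also exclude that participant.* This costs extra computation if the RQ1 cross-validation is not already nested. Ordinary out-of-fold predictions from RQ1 would meet the training condition but not the tuning and selection condition.

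Alternatively, keep one retrained model but exclude from retraining and tuning all entries by every author of a rated entry. If the 24 entries come from 24 authors with the average number of entries, this removes 24 × 10.08 ≈ 242 of 100 × 10.08 = 1,008 expected entries, and fewer if they come from fewer authors. Fully compliant authors would raise it to 24 × 14 = 336. The smaller training set would put the model at some disadvantage.

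In either case, state how the 24 entries are sampled across participants and whether the full dataset pools both groups. No new data are needed. The change should be settled before the model is retrained and compared with the experts.

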### Sample size calculation

4.1

In this NLP study, classical power analysis is not directly applicable, as the model performance depends on several factors such as training data points, model architecture, and transfer learning effects. Therefore, based on preceding transfer learning literature, 500 data points (D) per group (type and speak) are targeted [60, 61]. Each participant is expected to contribute one data point daily over the study duration of 14 days (d). A dropout rate of 28% (r) is assumed based on comparable studies [62–64]. The number of participants is calculated to be 50 participants per group (100 total):$$N=\frac{D}{d\times (1-r)}=\frac{500}{14\times (1-0.28)}\approx 49.6\approx 50$$

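### In RQ5 the MAE, RMSE and absolute-error comparisons of model and experts mix knowledge of this sample's score distribution with skill at reading journals; Spearman's rho does not

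*Protocol article*

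**What the plan says.** All references are to the protocol article.

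- **Metrics (4.2.6).** "Model and expert performance will be compared on item-level absolute errors using RMSE, MAE"; the sentence goes on to add Spearman's rho and pairwise tests. The bootstrap intervals are assigned to the MAE and RMSE differences. No metric is named as the deciding one.
- **Model (4.2.6).** The best model is "retrained with optimized hyperparameters on the full dataset, excluding the expert-rated entries".
- **Experts (3.7).** Each expert rates 24 entries on sliders that run over the questionnaire range. Ground truth comes at the end, as an incentive: "the journal entries will be presented again, along with their corresponding ground truth values, allowing the experts to compare their own assessments". No score distribution, labelled example or practice item before rating is described.
- **Zero-skill reference (4.2.2).** "As a baseline, a mean predictor will be implemented" appears under RQ1; 4.2.6 does not mention it.
- **Scales (3.4.3).** The MDBF and PSS-4 are both adapted to cover the whole past day.
- **Status (sections 2 and 3.7).** RQ5 is exploratory. Section 3.1 describes it as a practical benchmark for the models.

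**The concern.** Absolute error has two sources: poor ranking of entries, and wrong placement on the scale through an offset or too wide a spread. Supervised training gives the model this sample's mean and teaches it to pull uncertain predictions towards that mean. As described, the experts start from the slider end points. Familiarity with the momentary versions of the questionnaires need not tell them where students usually score on the whole-day versions.

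Two raters who extract the same information from a text can therefore differ on MAE and RMSE, and a constant guess at the mean can beat a skilled but miscalibrated expert. What is at stake is how the human benchmark is read. A model ahead of clinicians on MAE might only know the sample's distribution. Section 4.2.6 does not say how to read MAE and rho if they disagree. This issue is separate from whether the rated authors' other entries are in the training data; it would remain if all of them were held out.

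**Working it through.** **1. Size of the training set (4.1).** The target is "500 data points (D) per group (type and speak) are targeted", with 14 days and 28% dropout.
- The plan's own figure: 500 / (14 × 0.72) = 49.6, so 50 per group. Reproduced.
- Expected entries: 2 × 50 × 14 × 0.72 = 1,008, or 504 per group.
- Pooled, less the rated entries: 1,008 − 24 = 984.
- Group-specific: between 504 − 24 = 480 and 504, depending on which group the rated entries come from. Section 4.2.2 trains the groups separately, so either reading of the full dataset is possible.

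**2. Formulas.** Let SD be the standard deviation of the true score, r the correlation with truth, SDe the SD of the expert's ratings and b the expert's mean offset.
- Calibrated model: RMSE = SD × √(1 − r²)
- Mean predictor: RMSE = SD
- Expert: RMSE = √(SD² + SDe² − 2·r·SD·SDe + b²)

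The documents give none of SD, r, SDe or b. All are assumptions, shown over a range.

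**3. RMSE with SD = 1.2 on the 1–7 MDBF scale and the same r for model and expert** (excess over the model in brackets):

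| | r = 0.4 | r = 0.5 | r = 0.6 |
|---|---|---|---|
| Model | 1.10 | 1.04 | 0.96 |
| Mean predictor | 1.20 | 1.20 | 1.20 |
| Expert, SDe = 1.2, b = 0 | 1.31 (20%) | 1.20 (15%) | 1.07 (12%) |
| Expert, SDe = 1.2, b = 0.5 | 1.41 (28%) | 1.30 (25%) | 1.18 (23%) |
| Expert, SDe = 1.5, b = 0.5 | 1.58 (44%) | 1.46 (41%) | 1.33 (39%) |

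Worked cell, r = 0.5, SDe = 1.5, b = 0.5: √(1.44 + 2.25 − 1.80 + 0.25) = √2.14 = 1.46, and 1.46 / 1.04 = 1.41.

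**4. Boundary cases.**
- With SDe = SD and b = 0, the expert's squared error is SD²(2 − 2r). The expert beats the mean predictor only if r exceeds 0.5.
- With SDe = r × SD and b = 0, it is SD²(1 − r²), the same as the model. Ideal shrinkage removes the excess.
- A skilled, unbiased expert loses little: r = 0.8, SDe = SD and b = 0 is tied by a model with r = √(1 − 0.4) = 0.775.

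**5. Simulation on 24 independent entries.** One expert against a calibrated model, paired t-test at two-sided 0.05, 20,000 runs (4,000 for rho). Offsets here are in SD units. Equal skill, r = 0.6:

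| Expert spread ratio, offset | Model has lower MAE | Model significantly better | Model has higher rho |
|---|---|---|---|
| 1.0, 0 | 71% | 8% | 50% |
| 1.0, 0.5 | 89% | 20% | 50% |
| 1.3, 0.5 | 96% | 38% | 50% |

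After linear recalibration of the expert, the model has the lower MAE in 49 to 51% of runs and is significantly better in about 2.5%. That recalibration used the true shrinkage factor; one estimated from 24 entries would be noisier.

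The ranking can also reverse. A weaker model (r = 0.4) against a better but miscalibrated expert (r = 0.7, spread ratio 1.3, offset 0.5 SD) has the lower MAE in 75% of runs and the higher rho in only 8%.

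**The case against.** The strongest reply is that the same sentence already plans Spearman's rho. Offset and linear over-dispersion cannot change it, so a model ahead on MAE but not on rho would itself reveal miscalibration. This stands, and it confines the problem to MAE, RMSE, the absolute-error tests and the bootstrap intervals. It does not remove the problem: 4.2.6 attaches the item-level comparison to absolute errors and the bootstrap intervals to MAE and RMSE, and it names no deciding metric.

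Second, RQ5 is exploratory, with no superiority hypothesis or decision rule, and how clinicians rate without sample statistics is a legitimate practical question. This also stands. A reader might infer that the plan commits to claiming the model beats clinicians, or that the whole of RQ5 is decided by calibration. The documents support neither.

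Third, a reader might infer that experts never see a labelled example. Section 3.7 shows only that none is described before rating; labels follow afterwards, and an article may condense the survey instructions. Likewise, the mean predictor is planned under RQ1 and is merely not mentioned under RQ5.

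Fourth, recalibrating only the experts on the rated entries would give them label information that the model is denied. This is right, and any recalibration must be applied to both sides.

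**Conclusion.** The point holds for the absolute-error results of RQ5, not for RQ5 as a whole. At equal correlation with the truth, the expert's RMSE excess is about 12 to 44% over the assumed range and close to zero for an expert who shrinks ideally with no offset. Whether real experts are miscalibrated cannot be known from the documents, and the model is assumed to be well calibrated on the 24 entries.

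A reader might infer that an equally skilled model would look clearly superior. That is too strong: with one expert and 24 entries, the simulated model was significantly better in 8 to 38% of runs, although it had the lower MAE in 71 to 96%. The consequence is for interpreting an exploratory benchmark. The change is still worth making, because it is cheap and allows RQ5 to separate scale knowledge from reading skill.

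**What to change.** In section 4.2.6:

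1. Report the RQ1 mean predictor on the same 24 entries as a third comparator, for each MDBF subscale and the PSS-4.
2. Report the model–expert difference in Spearman's rho with a bootstrap interval. State that no conclusion that the model matches or beats experts will rest on MAE or RMSE alone when rho does not agree.
3. As a sensitivity analysis, report MAE and RMSE after the same cross-fitted linear recalibration of both expert and model scores, and say that it is imprecise with 24 entries.

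Showing experts the sample means and SDs or a few labelled practice entries is optional. At 1.5 minutes per entry the ratings take 24 × 1.5 = 36 of about 45 minutes, so there is room, but it changes the benchmark from naive to trained raters.

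The cost is a few lines of analysis and a more cautious reading of MAE and RMSE. Items 1 to 3 need no new data.

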### Data management

4.3

#### Handling of missing data and dropout

4.3.1

Incomplete daily records will not be used for analysis. Specifically, if a participant provides only a journal entry or only a daily questionnaire for a given day, that day’s data point will be excluded from the dataset. Missing data will not be imputed, as journal entries and subjective reports cannot be reliably reconstructed. Instead, the extent and patterns of missingness will be explored descriptively to assess whether data are missing at random or show systematic trends (e.g., participant characteristics, or study phase). Participant dropout will be recorded, including the timing and, where possible, reasons for discontinuation. Dropout has been accounted for in the sample size calculation.

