During the 14-day study phase, participants will be asked to record a daily journal entry as a (voice) message in the messenger service app, sharing their “high- and low-lights” of the day by either typing or speaking according to their group assignment. They will receive a notification via the messenger service around 6 p.m., but the assessment may be completed at any time during the remainder of their day. Immediately after creating the journal entry, participants will be asked to complete a short reflective survey on the SoSci Survey platform, accessed via an individualized link provided in the reminder message. Since the links will be personalized, all reminders will be sent individually and manually by the study team. The sequence—first journaling, then completing the questionnaire—is chosen to ensure that participants can report naturally on topics they consider relevant, without potential bias introduced by answering questionnaires beforehand. All questionnaire scores will serve as ground truth reference values for training and evaluating the NLP models. The total time required for journaling and survey completion is expected to be approximately 5–10 minutes per day. Each daily data point will include a journal entry, three emotional well-being metrics, a daily stress level, a measure of situational self-control, and a list of topics mentioned in the journal entry. To enhance compliance, the study team will monitor on a daily basis whether participants have completed the required assessment. If an assessment is missed or remains incomplete from the previous day, a reminder will be sent in the afternoon notifying the participant of the missed entry. The reminder will also include a brief question regarding the reason for the omission, along with an encouragement to complete the assessments on subsequent days. After the two-week study period, participants will receive individualized feedback based on their journal entries and questionnaire responses (see Section 3.5 for more detail). Providing it once at the end of the study was intended as an incentive to complete the two weeks. As a final step, participants will be asked to complete a feedback questionnaire to provide direct evaluations of their study experience. In addition, focus group sessions with voluntary participants will be conducted to further explore participant perspectives (see Section 3.6 for further details).

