#### Baseline assessment

4.2.1

Baseline questionnaire data will be summarized descriptively, and Spearman’s rank correlations will examine relationships between DASS-21 subscales, WHO-5, and SCS-K-D scores. Differences by sex and randomized group (type vs. speak) will be explored using two-way ANOVA. *P*-values will be reported for reference, but the study is not powered to detect baseline differences.

Daily measures of mood (MDBF subscales), stress (PSS-4), and state self-control (SSCCS) will be analyzed using linear mixed-effects models with random intercepts for participants to account for repeated measurements. Baseline well-being measures (SCS-K-D, DASS-21, WHO-5) and group assignment will be included as fixed effects to explore whether baseline characteristics predict daily mood and self-control. Daily observations will be included only for days with completed journals; the models naturally handle these unbalanced repeated measures. Additionally, person-level averages of daily mood and state self-control may be correlated with baseline measures using Spearman’s rank correlation as a descriptive check.

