#### RQ4: exploratory analysis of well-being

4.2.5

To explore whether emotional well-being and stress change over the 14-day study period and whether these changes differ between the type and speak groups, a mixed-effects model will be used. Fixed effects will include group, day, and their interaction (Day × Group). Random intercepts and slopes for participants will account for within-subject variability and individual trajectories.

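### The missing-data check in Section 4.3.1 cannot establish missing at random, on which the RQ4 time trend depends, so skipping that tracks daily mood and increases over the 14 days could pass as improvement

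*Protocol article*

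**What the plan says.** Section 4.3.1 (Handling of missing data and dropout) excludes any day on which the journal or the questionnaire is missing and rules out imputation. In its place, "the extent and patterns of missingness will be explored descriptively to assess whether data are missing at random or show systematic trends". The examples given are participant characteristics and study phase. Dropout is recorded with its timing and, where possible, its reasons.

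Section 3.3 (Procedure) describes the follow-up of a missed day: "The reminder will also include a brief question regarding the reason for the omission". The article states no analytic use for these answers.

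Section 4.2.5 sets out RQ4: "To explore whether emotional well-being and stress change over the 14-day study period", and whether the change differs between typing and speaking. The model has fixed effects for group, day and Day × Group, with random intercepts and slopes for participants.

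Section 4.2.4 (RQ3) models daily completion by mixed-effects logistic regression on group, day, trait and mean state self-control, and relevant interactions.

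Section 4.1 gives the only figure for data loss: "A dropout rate of 28% (r) is assumed based on comparable studies".

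**The concern.** Missing at random and missing not at random differ only in whether missingness depends on values that were not recorded. A description of recorded data cannot choose between them. The contrast in Section 4.3.1 is also misdrawn: a trend by participant characteristics or study phase is fully compatible with missing at random, provided the analysis conditions on those variables.

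This matters most for RQ4. A likelihood-based mixed model on completed days recovers the time trend under missing at random, but not if a student skips an evening because that day was bad. If such skipping grows over the two weeks, the completed days become increasingly selected towards good ones and the fitted trend rises with no true change. The Discussion already anticipates that journaling may itself improve well-being, so an artefact of this kind could be read as that effect. The descriptive look at patterns is the only safeguard Section 4.3.1 states.

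**Working it through.** **1. The plan's own figure.** Section 4.1: N = D / (d × (1 − r)) = 500 / (14 × 0.72) = 500 / 10.08 = 49.6, rounded to 50 per group. This reproduces. It implies 50 × 14 = 700 person-days per group, of which 700 × 0.72 = 504 are usable and 196 missing. The 28% is a dropout rate; the article gives it no time course and no link to mood.

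**2. What the planned checks can show.**
- Missing completely at random: skipping is unrelated to anything. Observed patterns can contradict this.
- Missing at random: skipping depends only on recorded data. Trends by characteristics, group or day fit here.
- Missing not at random: skipping also depends on that day's unrecorded mood. Observed patterns may look the same as in the second case.

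The RQ3 compliance model adds a formal view of missingness by group and day. It has no term for the mood of a missed day, because that mood was not recorded.

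**3. Size of a possible false trend.** Assumptions, none of them from the documents: true change zero; within- and between-person SD 0.9 on the 1 to 7 MDBF scale; odds of skipping multiplied by OR for each SD of worse mood that day. Let e be the day's deviation from the person's own level, a(t) the log-odds of skipping on an average day, and p(t) the corresponding proportion missed.

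logit P(skip on day t) = a(t) − ln(OR) × e / 0.9

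Mean deviation on completed days = E[e × (1 − P)] / E[1 − P], which to first order is 0.9 × ln(OR) × p(t).

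False change, day 1 to day 14, to first order = 0.9 × ln(OR) × [p(14) − p(1)]. For example, OR 1.5 with 10% to 45%: 0.9 × 0.405 × 0.35 = 0.128. This overstates strong dependence, so the exact expectation by numerical integration is shown beside it.

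| Missed days, day 1 to day 14 | OR | First order | Exact expectation |
|---|---|---|---|
| 10% to 45% | 1.5 | +0.128 | +0.121 |
| 10% to 45% | 2 | +0.218 | +0.187 |
| 10% to 45% | 3 | +0.346 | +0.245 |
| 20% to 36% | 1.5 | +0.058 | +0.055 |
| 20% to 36% | 2 | +0.100 | +0.083 |
| 20% to 36% | 3 | +0.158 | +0.107 |
| 28% throughout | 1.5 to 3 | 0 | 0 |

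Mixed models fitted to simulated data (100 students, 14 days) agree within simulation error: about +0.12 to +0.25 for the steep rise, +0.04 to +0.11 for the gentle rise, and about 0 at a constant rate. When skipping ignores mood, the change is also about 0.

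**4. Selectivity rising instead of frequency.** Assumed SDs: 0.8 between persons, 1.0 day to day, 0.03 per day for the random slope. About 28% of days are missed overall, and mood dependence grows from none on day 1 to twice 0.5 or 1.0 log-odds per point on day 14. The false gain is +0.25 to +0.42 points.

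**5. Against the precision of the trend.** The standard error of the day 1 to day 14 change is about 0.09 with a random intercept only. In the steep case, 23%, 50% and 77% of runs are then nominally significant for OR 1.5, 2 and 3; in the gentle case, 9%, 16% and 18%. With random slopes as Section 4.2.5 specifies (assumed slope SD 0.5 to 0.8 points over the study), the steep case falls to 14–17%, 29–38% and 51–65%.

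**The case against.** The authors probably mean random in the everyday sense, as opposed to systematic; descriptive patterns can speak to that. This is a fair reading of intent, but a check for missing completely at random leaves untested the assumption that RQ4 needs.

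Several stronger readings are tempting, and the documents do not support them:
- *The plan ignores the omission reasons.* The article states no use for them. Its list of patterns is introduced as examples, so their use is not excluded.
- *Nothing planned would reveal differential or rising missingness.* The RQ3 model includes group and day and will show both. Only dependence on that day's mood stays hidden.
- *The plan claims that its mixed models cure the problem in RQ4.* The phrase "the models naturally handle these unbalanced repeated measures" stands in Section 4.2.1 and concerns models of daily measures on baseline scores. It speaks of unbalanced data and asserts nothing about the missingness mechanism.
- *Bad-day skipping is the likely mechanism.* No passage says so. It is a possibility that the plan cannot rule out.
- *Bad-day skipping by itself creates a false trend.* At constant rate and selectivity it raises the mood level (by about 0.10 to 0.26 points for OR 1.5 to 3 with about 28% missed on an average day) but leaves the slope at zero.
- *The typing versus speaking comparison is biased.* This requires mood-dependent skipping to differ by group. If only one group skipped on bad days, with skipping rising over time, simulation gave a Day × Group bias of +0.19 to +0.26 points but rejection in only 12–20% of runs against 5%. The documents give no reason to assume this.

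It is also true that a detailed sensitivity analysis is commonly left to an analysis plan. Its absence from the article is not the defect; the defect is the stated purpose of the check.

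**Conclusion.** The point holds as a minor one. Section 4.3.1 assigns to a descriptive check a question it cannot answer, and RQ4 rests on that question. A false improvement needs two conditions together: skipping related to that day's mood, and skipping that grows in frequency or selectivity over the 14 days. Given both, with the assumed SDs of 0.9 and odds ratios of 1.5 to 3, the false gain is about +0.04 to +0.11 points for a 20% to 36% rise and +0.12 to +0.25 for a 10% to 45% rise. Without the second condition there is no false trend. The SDs, odds ratios and time courses are all assumptions; the documents supply only the 14 days, the sample of 100, the scale and the 28%.

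RQ4 is labelled exploratory, and the article ties further work to RQ1 and RQ2, so no confirmatory conclusion is at risk. The sample size figure is unaffected.

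**What to change.** 1. In Section 4.3.1, replace the stated purpose with: *to describe whether missingness is related to observed characteristics, group or study day*. Add that RQ4 assumes missing at random and that this cannot be verified from the observed data.
2. Tabulate the omission reasons already requested in the reminders, together with the discontinuation reasons, by group and study day, classed as mood- or stress-related versus logistical.
3. For RQ4 only, add one exploratory delta-adjusted (pattern-mixture) sensitivity analysis. Shift the missed days' MDBF and PSS-4 over a fixed range of worse values (for instance 0.25 to 1.0 MDBF point), in both groups and then in one group at a time, and report where the conclusion changes. This may sit in the analysis plan. The no-imputation rule stays for the NLP data.

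The cost is a change of wording, one table and one extra analysis, with no new data and no added burden on participants. The downside is a little more work and possibly a less firm statement on RQ4.
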